## Abstract

**Objective:**

To evaluate the efficacy of transcranial direct current stimulation (tDCS) in reducing the incidence of postoperative delirium (POD) in elderly patients undergoing hip fracture surgery.

**Methods and analysis:**

This single-center, double-blind, randomized controlled trial will enroll 160 participants aged 65 years and older, scheduled for elective hip surgery under spinal anesthesia. Participants will be randomly assigned to either the active-tDCS group or the sham-tDCS group. The active-tDCS group will receive two sessions: one pre-surgery and one post-surgery, with electrodes positioned over the left dorsolateral prefrontal cortex and the right supraorbital area. Each session includes 15-second ramp-up phase at the start, 20 min simulation with 2 mA current and 15-second ramp-down phase at the end. The sham-tDCS group will receive two sham procedures with no actual current delivered. Functional brain activity will be monitored before and after each session or sham procedure to assess changes in cortical activation and connectivity using functional near-infrared spectroscopy (fNIRS). The primary outcome measure will be the incidence of POD, assessed using the 3-Min Diagnostic Interview for Confusion Assessment Method (3D-CAM). Secondary outcomes include the severity of delirium, postoperative pain, anxiety, depression, cognitive function, and sleep quality.

**Trial registration:**

The trial was registered at ClinicalTrials.gov (NCT06678529) on Oct 22, 2024.

## Introduction

Post-operative delirium (POD) is a common complication in elderly patients (1). The incidence of POD varies by surgical type and invasiveness. More invasive, extensive procedures typically lead to higher POD rates than less invasive, shorter ones (2). POD can affect the prognosis of patients and even increase the mortality rate. However, as of now, the available effective treatments for postoperative delirium remain limited. Hence, it is crucial to identify efficacious interventions that can prevent this condition.

Transcranial direct current stimulation (tDCS) is a non-invasive neuromodulation technique that can alter cortical excitability and the spontaneous electrical activity of neurons (3). This method has been shown to enhance the functional connectivity of key regions within the left frontoparietal sensorimotor network, as well as neural circuits involved in consciousness regulation (4). Evidence supports the use of tDCS in improving various cognitive functions, including memory, attention, and perception (5). A study by Tao et al. demonstrated that a single session of left dorsolateral prefrontal tDCS significantly reduced the incidence of postoperative delirium in elderly patients undergoing lower limb joint replacement under general anesthesia, with rates decreasing from 19.7% to 4.9% (6). Functional near-infrared spectroscopy (fNIRS) is an emerging brain imaging modality that offers high spatial and temporal resolution, along with resistance to motion artifacts and electromagnetic interference (7). It is a safe, non-invasive, and user-friendly technology that enables real-time monitoring, making it particularly promising for applications in neurocognitive assessment, clinical diagnostics, and rehabilitation (8). fNIRS works by quantifying changes in blood oxygenation within brain tissue, using the absorption and scattering of near-infrared light, with data processed via the Beer-Lambert Law (9). This technique indirectly reflects neural activity, enabling real-time evaluations of brain function, and may serve as a biomarker for the early detection of delirium, offering a novel tool for monitoring postoperative cognitive status.

In elderly patients, particularly those with cardiopulmonary comorbidities, spinal anesthesia is increasingly preferred over general anesthesia for hip fracture surgery, although there is no significant difference in the effect of spinal anesthesia and general anesthesia on postoperative delirium (10, 11). The aim of this study is to conduct a randomized, controlled, double-blind trial to (1) evaluate the potential of tDCS in reducing the incidence of postoperative delirium in elderly patients undergoing hip fracture surgery under spinal anesthesia, and (2) use fNIRS to investigate the mechanisms through which tDCS modulates brain network connectivity, brain region activation, and the reduction of POD. This investigation seeks to provide clinical evidence supporting the use of tDCS as an intervention to mitigate postoperative delirium in this vulnerable patient population.

## Materials and methods

### Study design

This study is a prospective, single-center, double-blind, randomized controlled trial, conducted in accordance with the Standard Protocol Items: Recommendations for Interventional Trials (SPIRIT) guidelines (12). The trial staff will review orthopedic inpatient registration lists and elective surgery application forms to identify adults aged 65 years and older scheduled for surgical repair of clinically or radiologically diagnosed femoral neck, intertrochanteric, or sub-trochanteric hip fractures. Potential participants will be screened for eligibility based on inclusion and exclusion criteria, which will be assessed through medical record reviews and face-to-face interviews. The study design is depicted in Figure 1, and the trial schedule is outlined in Table 1.

**Figure 1 F1:**
[figure not shown]
Trial flow chart. tDCS, transcranial direct current stimulation; ITT, intention-to-treat; PP, per-protocol.

**Table 1 T1:** Time schedule of the trial process.

**Item**	**T0**	**Pre-surgery**			**Post-surgery**						

		**f1**	**1st tDCS**	**f2**	**f3**	**2nd tDCS**	**f4**	**Day 1**	**Day 2**	**Day 3**	**Day 5**
Enrolment											
Informed consent	×										
Eligibility screen	×										
Demographics	×										
Diagnosis	×										
Comorbidities	×										
Frailty scale	×										
ASA grade	×										
MMSE	×										×
GAD-7	×							×		×	
PHQ-9	×							×		×	
Laboratory tests	×										
Randomization	×										
Interventions		×	×	×	×	×	×				
Assessments											
3D-CAM^*^	×							×	×	×	
NRS	×							×	×	×	×
Analgesia								×	×	×	
PSQI	×							×	×	×	
Complications											×

The four functional near-infrared spectroscopy (fNIRS) assessments will be conducted at specific time points before and after transcranial direct current stimulation (tDCS) as follows: (1) pre-surgery, pre-tDCS (f1): the first fNIRS measurement will be obtained prior to surgery, before the first application of tDCS; (2) pre-surgery, post first tDCS (f2): the second fNIRS measurement will be performed before surgery, following the first application of tDCS; (3) post-surgery, before second tDCS (f3): the third fNIRS measurement will be conducted after surgery, before the second application of tDCS; (4) post-surgery, post second tDCS (f4): the fourth fNIRS measurement will be taken after surgery, following the second application of tDCS. ASA, American Society of Anesthesiologists; MMSE, Mini-Mental State Examination; GAD-7, Generalized Anxiety Disorder-7; 3D-CAM, 3-min diagnostic interview for Confusion Assessment Method; PHQ-9, Patient Health Questionnaire-9; ^*^indicates twice a day, once in the morning and once in the afternoon; NRS, Numeric Rating Scale; PSQI, Pittsburgh Sleep Quality Index.

### Ethics approval and consent

The study will be conducted in full compliance with relevant regulations, including the Declaration of Helsinki as set forth by the World Medical Association. Prior to initiation, the research protocol will be reviewed and approved by the Institutional Review Board. Before enrollment, the investigators will thoroughly explain the study's objectives, procedures, and potential risks to each participant or their legal representative. Written informed consent will be obtained from all participants, ensuring they understand their right to withdraw from the study at any time without consequence. Informed consent documents will be retained as part of the clinical research records. Throughout the duration of the study, participant privacy and data confidentiality will be strictly maintained. This study has been approved by the Institutional Review Board of Shanxi Bethune Hospital (approval number YXLL2024191) and is registered on ClinicalTrials.gov (registration number NCT06678529).

### Inclusion criteria

Participants will eligible to participate in this study after meeting all of the following criteria: (1) aged ≥ 65 years; (2) scheduled for elective hip fracture, including femoral head fractures, femoral neck fractures, intertrochanteric or sub-trochanteric fractures, femoral head replacement, total hip arthroplasty, or open or closed reduction; (3) platelet count >80 × 10^9^/L; (4) ASA classification ≤ Grade III; (5) Mini-Mental State Examination (MMSE) scores ≥ 18 points (13); (6) willingness to participate and sign the informed consent form.

### Exclusion criteria

Participants will be excluded from this study if they meet any of the following criteria: (1) severe mental disorders (e.g., depression or schizophrenia requiring medication treatment); (2) cranial or scalp injuries; (3) history of symptomatic cerebrovascular disease, including stroke, transient ischemic attack; (4) compound injuries, multiple fractures, periprosthetic fractures, and hip joint revisions; (5) drug or alcohol abuse; (6) severe visual or hearing impairments; (7) history of epilepsy or intracranial metal implants; (8) severe cardiovascular disease history and liver dysfunction, or kidney dysfunction; (9) coagulation abnormalities; (10) severe chronic obstructive pulmonary disease; and (11) participation in other clinical studies within the past 3 months.

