### Follow-up

Delirium will be assessed during the first three post-operative days, along with pain at rest and during movement and the dosage of analgesics. On the fifth post-operative day, assessments will include the MMSE and the occurrence of any complications. The primary endpoint of the study is the completion of cognitive evaluation on postoperative day five. Delirium will be assessed by trained specialists, who will undergo a rigorous training and receive comprehensive guidance from expert psychiatric consultants prior to the commencement of the trial. Delirium will be evaluated twice daily during the first three post-operative days. The assessment time points will be scheduled from 9:00 AM to 11:00 AM and 3:00 PM to 5:00 PM, ensuring a minimum interval of 6 h between assessments. POD will be assessed using a 3-min diagnostic interview (3D-CAM) conducted by researchers who were blinded to the study group allocation. The Confusion Assessment Method (CAM) assessment is based on the four key features of delirium: acute onset and fluctuating course, disorganized thinking, inattention, and altered levels of consciousness. Investigators will also consult the medical record or contact a family member, friend, or health care provider who knows the patient well to gather additional information regarding the patient's symptoms. If POD is identified, daily assessments will continue until symptoms resolve or the patient is discharged. Delirium subtypes will be assessed using the Richmond Agitation Sedation Scale (RASS) (17). Hyperactive delirium is characterized by symptoms ranging from mild restlessness to persistent motor activity and irritability. Conversely, hypoactive delirium is characterized by one or more of the following features: reduced or absent movement, minimal verbal communication despite stimulation, and a lack of responsiveness. Mixed delirium is characterized by rapid fluctuations between the hyperactive and hypoactive states. The severity of delirium will be assessed using the Delirium Rating Scale Revised-98 (DRS-R-98) (18).

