### Clinical outcomes and assessments

The primary outcome of this study is the occurrence rate of delirium on post-operative days 1, 2, and 3. Secondary outcomes include the severity of POD, pain scores at rest and during movement, anxiety and depression scores, sleep quality, as well as post-operative cognitive function and complications. Another key outcome is the change of whole brain cortical networks and brain activation patterns during resting state and verbal fluency tasks.

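### Delirium is assessed at T0, but nothing excludes a patient who is already delirious, so pre-existing delirium can count as postoperative delirium

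*Protocol article*

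**What the plan says.** - **Schedule.** Table 1 marks the 3D-CAM at T0 and on Days 1, 2 and 3. The row stands under assessments, separate from the eligibility screen.
- **Exclusion criteria.** "Participants will be excluded from this study if they meet any of the following criteria: (1) severe mental disorders" begins a numbered list of eleven items. The nearest to delirium is "severe mental disorders (e.g., depression or schizophrenia requiring medication treatment", which concerns psychiatric illness under medication.
- **Inclusion criteria.** Six items. Two bear indirectly on delirium: "Mini-Mental State Examination (MMSE) scores ≥ 18 points" and "willingness to participate and sign the informed consent form".
- **Primary outcome (Clinical outcomes and assessments).** "The primary outcome of this study is the occurrence rate of delirium on post-operative days 1, 2, and 3". There is no new-onset condition.
- **Follow-up.** "Delirium will be evaluated twice daily during the first three post-operative days". This section describes postoperative assessments only.
- **Baseline characteristics.** The T0 3D-CAM is not among the variables listed.
- **Statistical analysis.** It fixes one special case, a refused delirium assessment (counted as delirium), but does not mention a participant who was positive at T0.

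**The concern.** The trial asks whether tDCS prevents postoperative delirium. Both sessions are given on the day of surgery, after T0, so they cannot prevent delirium that is already present at T0. The eligibility lists are given as complete lists and let such a patient in. The outcome definition then counts the patient if the delirium persists into days 1 to 3.

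The result is a mixture of prevalent and incident delirium. The planning rates in the Sample size section (about 20%, and 19.7% falling to 4.9%) are rates of postoperative delirium and make no allowance for cases carried in from before surgery. At stake are an outcome that does not match the question, a relative risk diluted towards 1, and a loss of power in a trial with little to spare.

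**Working it through.** **Inputs from the Sample size section:** 19.7% (control) and 4.9% (active); about 20% from the meta-analysis; two-sided alpha 0.05; power 0.80; 71 per group, raised to 80 for 10% loss.

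**Input not in the documents:** m, the share of each arm that is delirious at T0 and still positive in the days 1 to 3 window. This is an assumption, shown over 0 to 15%.

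**Step 1. Reproduce the plan's figure.** With the unpooled normal approximation and 20% against 4.9%:

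n = (0.20 × 0.80 + 0.049 × 0.951) × (1.960 + 0.842)² / (0.20 − 0.049)² = 71.1 per group.

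This agrees with the stated 71. Allowing for loss, 71 / 0.9 = 79, consistent with 80. The sample size itself is not in dispute here.

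**Step 2. Observed rates with prevalent cases counted.** In each arm, observed rate = m + (1 − m) × p, with p = 0.197 or 0.049. Example for m = 5%:
- control: 0.05 + 0.95 × 0.197 = 0.237
- active: 0.05 + 0.95 × 0.049 = 0.097 (0.0966 before rounding)
- relative risk: 0.0966 / 0.237 = 0.41

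**Step 3. Power.** Exact power of the two-sided Pearson chi-square test, obtained by summing the binomial probabilities of all tables that reject at 0.05:

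| m | Control | Active | RR | Power, 80 per arm | Power, 71 per arm |
|---|---|---|---|---|---|
| 0 | 19.7% | 4.9% | 0.25 | 84.5% | 80.0% |
| 1% | 20.5% | 5.9% | 0.29 | 80.8% | 76.0% |
| 2% | 21.3% | 6.8% | 0.32 | 77.2% | 72.3% |
| 3% | 22.1% | 7.8% | 0.35 | 73.7% | 68.9% |
| 5% | 23.7% | 9.7% | 0.41 | 67.4% | 62.8% |
| 10% | 27.7% | 14.4% | 0.52 | 55.1% | 50.5% |
| 15% | 31.8% | 19.2% | 0.60 | 45.6% | 41.3% |

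A pooled normal approximation tells the same story: at 80 per arm, 82% with m = 0, 76% at 2%, 67% at 5% and 45% at 15%. On that approximation, restoring 80% power would take 110 per arm at m = 5% and 146 at m = 10%, before loss.

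**Step 4. Cost of setting these patients aside instead.** If 5% of 80 per arm are T0-positive and are left out of the primary analysis, 80 × 0.95 = 76 remain. Exact power at 76 per arm with 19.7% against 4.9% is 82.8%, compared with 67.4% if they are kept and all counted as events.

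**The case against.** - **The prevalence is unknown, and the filters lower it.** Nothing in the documents supports 10% or 15%. MMSE of at least 18, personal consent, and the exclusions for stroke, substance abuse and severe sensory impairment will all keep out some delirious patients, and the fNIRS verbal task presupposes a cooperative one. This stands. It makes the lower rows of the table the more plausible ones, but none of these filters is a delirium criterion. The MMSE threshold is a global cognitive score, whereas the article's own description of delirium rests on acute onset and fluctuation, inattention, disorganised thinking and altered consciousness. Fluctuating delirium is compatible with a score of 18 or more.
- **The model is worst case.** It assumes that tDCS does nothing for these patients. Raw T0 prevalence also exceeds m. If only half of T0-positive patients stay positive and the rest have no event, exact power at 80 per arm is 78% for a 3% prevalence and 74% for 5%. This stands as a limit on size.
- **The Abstract and the Sample size section speak of incidence**, which may signal that new cases were intended. That is fair as a reading of intent, but no operational rule carries it out.
- **Handling of T0-positive participants in the analysis may be left to an analysis plan.** Accepted. The point therefore rests on the eligibility lists and the primary outcome wording, both of which belong to the protocol and are stated in it.
- **Consent by proxy.** Ethics approval and consent has the study explained "to each participant or their legal representative", but the same section requires written consent from all participants. This is weak evidence that delirious patients could enter, and the conclusion does not depend on it.
- **The effect is conservative.** True: equal numbers in both arms are expected, though not guaranteed, and neither arm is favoured. A diluted estimate and a missed effect are still failures for a trial of this size.

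**Conclusion.** The concern holds. Followed literally, the plan admits a patient who is delirious at T0 and counts persisting delirium as a primary event, although the measurement that would prevent this is already scheduled.

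The absence of a criterion is certain. The size depends on m, which the documents do not give. If the planning rates are right for new delirium and prevalent cases behave alike in both arms, 2% is enough to take power below the 80% target even with all 80 per arm evaluable (77%), and at the planned 71 evaluable even 1% is enough (76%). At 5% the expected relative risk is 0.41 instead of 0.25 and power is 67%. The 10% and 15% rows show the direction only. Even with a very small m, the outcome as worded does not match the prevention question.

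**What to change.** 1. Add a positive 3D-CAM at T0 to the exclusion criteria, and move that assessment into the eligibility screen in Table 1.
2. State the primary outcome as new-onset delirium on days 1 to 3 among participants who were 3D-CAM negative at T0. If anyone positive at T0 has already been enrolled, analyse the full randomised set, including them, as a sensitivity analysis.
3. List T0 3D-CAM status among the baseline characteristics.
4. Record the change as a dated amendment before unblinding. T0 status is measured before the first session, so restricting on it leaves the randomised comparison intact; chosen after unblinding, it would be a post hoc change to the primary outcome.

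The cost is one eligibility line and one sentence in the outcome definition. No new assessment is needed. The downside is a few more patients screened and a slightly narrower population.

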### Termination criteria

The study will be terminated if a participant experiences conditions that make it inappropriate to continue their involvement in the study, including: (1) worsening of the participant's medical condition; (2) severe adverse events; and (3) poor compliance with study protocols. Additionally, the study may be terminated under the following circumstances: (1) discovery of serious safety issues by investigators; (2) substantial flaws or errors in the study protocol that affect the study's integrity or participant safety; (3) the sponsor decides to terminate the study due to financial constraints or management issues; and (4) administrative authorities revoke approval for the trial. Termination of the study may be either temporary or permanent. In the event of termination, all trial records must be preserved and retained for future reference.

### Randomization and blinding

An independent research coordinator will oversee randomization and group allocation. Randomization will be performed using Stata statistical software, and allocation concealment will be ensured through the sealed envelope method. Sequentially numbered, opaque black envelopes containing random allocation numbers will be prepared and stored at the research site. Enrolled participants will receive the envelope with the lowest available number, corresponding to their group assignment. On the day of surgery, after the participant has been admitted to the Post - Anesthesia Care Unit (PACU), the clinical research coordinator will open the assigned envelope, note the allocation, and assign the participant to the appropriate study group. The participant's identification number will be recorded. The physician administering tDCS will be informed of the participant's group allocation. This process will be repeated for each subsequent participant. Once an envelope has been opened, it will not be reused. If a participant withdraws from the study after the envelope has been opened, their data will still be included in the analysis, and the reason for withdrawal will be documented. All participants will remain blinded to their group assignment. Surgeons, anesthesiologists, and ward and operating room nurses will also be blinded to the group allocations and intervention protocols. Additionally, personnel involved in outcome assessment, follow-up, data collection, and data processing will remain blinded to both the intervention protocols and group assignments.

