### Interventions

The standard intervention consists of two sessions of tDCS and four sessions of fNIRS. The intervention timeline is depicted in Figure 2. The tDCS sessions will be administered on the day of surgery: the first session will be conducted preoperatively and the second session will take place postoperatively in the PACU. The fNIRS assessments will be performed as part of the monitoring protocol at four designated time points throughout the study.

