**Figure 2 F2:**

Timeline of the experimental design. tDCS, transcranial direct current stimulation; fNIRS, functional near-infrared spectroscopy.

The tDCS procedure is administered using a transcranial direct current stimulator, with two electrodes placed in physiological saline soaked sponges. The electrodes are secured with a stretchable cap, positioning the anode over the left dorsolateral prefrontal cortex (DLPFC) and the cathode over the right supraorbital area. The active-tDCS group will receive a 15-second ramp up phase at the start, 2 mA of tDCS for 20 min and a 15-second ramp down phase at the end. The sham-tDCS group will only receive the 15-second ramp up phase at the beginning and the 15-sencond ramp down phase at the end of each session, without the continuous 2 mA current for 20 min (6). Research personnel administering the intervention will closely monitor participants for any discomfort. If a participant experiences any intolerable discomfort, the stimulation will be immediately terminated.

Four fNIRS procedures will be conducted in relation to the tDCS interventions: (1) f_1_ (pre first tDCS) will be conducted before the first tDCS session; (2) f_2_ (post first tDCS, pre-surgery) will be conducted after the first tDCS session and before surgery; (3) f_3_ (post-surgery, before second tDCS) will be conducted after surgery and before the second tDCS session; (4) f_4_ (post second tDCS) will be conducted after the second tDCS session. The fNIRS device used is the NirSmartII-6000 A, a 41-channel system that includes 19 light emitting source probes and 16 detector probes. The system comprises near infrared light sources and avalanche photodiodes as detectors, with a sampling frequency of 11 Hz. This system continuously measures and records changes in the concentrations of oxygenated hemoglobin (HbO) and deoxygenated hemoglobin (HbR) in the brain during task performance. Relative concentration changes in HbO, HbR, and total hemoglobin (HbT) are calculated based on the modified Beer Lambert Law.

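### As written, the envelope is opened and the tDCS operator informed only after PACU admission, yet the first active or sham session, which differs by arm, is given before surgery.

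*Protocol article*

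**What the plan says.** The Randomization and blinding section describes sequentially numbered, opaque envelopes prepared in advance. Each enrolled participant is given the lowest-numbered one left. On the operative day, "after the participant has been admitted to the Post - Anesthesia Care Unit (PACU), the clinical research coordinator will open the assigned envelope", and then "note the allocation, and assign the participant to the appropriate study group". The section continues: "The physician administering tDCS will be informed of the participant's group allocation". It describes no earlier opening and no earlier disclosure. On withdrawals it adds: "If a participant withdraws from the study after the envelope has been opened, their data will still be included in the analysis".

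The Interventions section places both sessions on the day of surgery: "the first session will be conducted preoperatively and the second session will take place postoperatively in the PACU". The Abstract agrees: "The active-tDCS group will receive two sessions: one pre-surgery and one post-surgery". In Table 1, f1, the first tDCS and f2 all stand under the pre-surgery heading. The row "Randomization" is marked at T0, the first column.

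The arms differ at both sessions. The Interventions section gives the sham group only the ramp phases, "at the end of each session, without the continuous 2 mA current for 20 min".

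**The concern.** The person delivering session 1 has to know whether to give active or sham stimulation. On the stated procedure that person is told only once the participant is in the PACU, and by then session 1 and the operation are over.

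Two things are at stake. If session 1 is given without reference to the allocation, it drops out of the randomised contrast. The trial would then compare arms on the second session only, although the sample-size section states the hypothesis in terms of two sessions, and the change from f1 to f2 would not be a randomised comparison. If session 1 is given by allocation, someone must have unsealed the envelope before surgery, and the published account of concealment is not the one used. With sealed envelopes, protection against selection depends on when the envelope is opened and by whom, so a reader needs that time to be right.

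**Working it through.** This is a check of event order. No formula is involved, the protocol gives no figure on this point to reproduce, and the sample-size calculation does not enter it.

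**Inputs**

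| Event | Stated time | Where |
|---|---|---|
| Randomization | T0 | Table 1 |
| f1, session 1, f2 | Before surgery | Table 1; Interventions; Abstract (session 1) |
| Envelope opened, group assigned | Day of surgery, after PACU admission | Randomization and blinding |
| Operator informed | Stated directly after the opening | Randomization and blinding |
| Session 2 | After surgery, in the PACU | Interventions |
| Arms differ | In each session | Interventions |

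**Order if the Randomization and blinding section is followed:** enrolment and numbered envelope → f1 → session 1 → f2 → surgery → PACU admission → envelope opened, group assigned, operator informed → session 2. The fourth fNIRS measurement follows session 2. The third falls between surgery and session 2, and the text does not place it relative to the opening.

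**Order if opening belongs to the T0 step in Table 1:** randomization → f1 → session 1 → f2 → surgery → f3 → session 2 → f4. This can be carried out, but it contradicts the stated opening time.

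**Extent under the first order**
- Sessions before opening: 1 of 2, i.e. 1/2 = 50%.
- fNIRS pairs around a session that are complete before opening: f1–f2, 1 of 2.
- Participants to whom the sequence applies: 80 + 80 = 160.

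**Is the group needed at session 1?** Yes. The sham description applies to every session, so session 1 cannot be identical in both arms without contradicting the Interventions section.

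**The case against.** The strongest defence is that the opening sentence says after PACU admission, not after surgery. The Interventions section gives no place for session 1, the PACU paragraph under Data collection says that the intervention is given there, and anaesthesia monitoring is required throughout the intervention. If patients went to the PACU before the operation, the conflict would vanish. Figure 2, the intervention timeline, is also not available here. This reading is possible but unsupported: the Interventions section ties only the postoperative session to the PACU, and nothing describes a preoperative PACU admission. If that is local practice, the text has to say so.

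Other parts of the defence stand, and they rule out stronger readings that a reader might infer.

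- **That no allocation exists before session 1.** It does. The envelopes are prepared beforehand, and each enrolled participant receives a numbered one. What comes late is opening, assignment and disclosure.
- **That Table 1 is a separate, irreconcilable conflict.** Randomization at T0 can mean handing out the numbered envelope, with opening as a later step. The firm conflict is between the opening time and the preoperative first session.
- **That participants lost between session 1 and the PACU are excluded from the intention-to-treat analysis.** The Interventions section keeps anyone unable to receive both sessions, for any reason. The Statistical analysis section keeps those who consent and then refuse the assigned intervention. The sentence on withdrawal after opening includes people; it does not say that others are left out.
- **That concealment was broken, or that session 1 was the same for everyone.** The document states neither, and the Abstract and Interventions sections show the opposite intent for session 1.

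**Conclusion.** The point holds as a contradiction within the protocol article that must be corrected. The randomisation procedure as written cannot deliver session 1 by concealed allocation. Its reach is the whole trial: for all 160 planned participants, one of two sessions and one of two fNIRS pairs precede the stated opening. Those counts describe the consequence of following that one sentence literally; they do not measure bias that has occurred.

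The conclusion assumes that PACU has its ordinary postoperative meaning, as the Interventions section uses it, and that no earlier disclosure to the operator is made in a document not shown. The quickest explanation may be a wording slip. Even so, this sentence is the only operational instruction for opening envelopes, and a reader cannot tell which order was used. The sample size and the definition of the analysis populations are not affected.

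**What to change.** Reconcile the opening time in Randomization and blinding with the Interventions section and Table 1. State that the independent coordinator opens the envelope and informs only the tDCS operator after consent, eligibility and enrolment and before the first session. Opening after f1 is preferable, because the baseline recording is then made before anyone knows the arm, but any time between enrolment and session 1 removes the contradiction. A short note to Table 1 can say whether its T0 entry means handing out the envelope or opening it.

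State also what was actually done for anyone already enrolled: when the envelope was opened, by whom, and how session 1 was assigned.

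No new intention-to-treat rule is needed. The existing sentence on withdrawal after opening would simply apply from the corrected time.

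The cost is about one sentence of amendment and a table note, with no added staff or participants. One small consequence is that a few participants whose surgery is cancelled after opening would remain in the intention-to-treat set.
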